### Safety reporting

#### Adverse events

AEs are defined as any undesirable experience occurring to a participant during the study, whether or not considered related to the experimental intervention. Given that hospitalised patients often experience AEs, only potential study-related AEs reported by the participant or observed by the study team during the timeframe of tACS treatment will be documented in the case report form. These include sensations related to tACS (ie, itch, pain, burn, heat, iron taste, headache, neck pain, phosphenes, dizziness and nausea), behaviour suggesting of increase in delirium severity such as increase in use of antipsychotics, patient fixation, falling out of bed and self-removal of a line, tube or drain, and a possible epileptic seizure. On each treatment day, the study team will screen the electronic patient record and consult with the treating physician or nurse about any health changes since the previous tACS session. Any event potentially related to the study procedures will be classified as an AE.

#### Serious adverse events (SAEs)

An SAE is any untoward medical occurrence or effect that

results in death;is life threatening (at the time of the event);requires hospitalisation or prolongation of existing inpatients’ hospitalisation;results in persistent or significant disability or incapacity;any other important medical event that did not result in any of the outcomes listed above due to medical or surgical intervention but could have been based on appropriate judgement by the investigator.

For the purpose of this study, an SAE is defined according to the definition above, within the timeframe of tACS treatment, which includes up to 24 hours after the last tACS session. It should be noted that infectious diseases such as pneumonia, wound infection, sepsis, (postoperative) haemorrhage, or laboratory disturbances, such as hyponatraemia or hypokalaemia that may prolong inpatients’ hospitalisation or may be life threatening, will not be considered as an SAE. This exclusion is due to the frequency of these complications in the population being studied, which is unrelated to tACS treatment.

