## Abstract

**Introduction:**

Delirium, a clinical manifestation of acute encephalopathy, is associated with extended hospitalisation, long-term cognitive dysfunction, increased mortality and high healthcare costs. Despite intensive research, there is still no targeted treatment. Delirium is characterised by electroencephalography (EEG) slowing, increased relative delta power and decreased functional connectivity. Recent studies suggest that transcranial alternating current stimulation (tACS) can entrain EEG activity, strengthen connectivity and improve cognitive functioning. Hence, tACS offers a potential treatment for augmenting EEG activity and reducing the duration of delirium. This study aims to evaluate the feasibility and assess the efficacy of tACS in reducing relative delta power.

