## Methods and analysis

### Study objectives

For the pilot phase, the primary objective is to evaluate the safety and tolerability of tACS in patients with delirium. The main study phase aims to determine the efficacy of a single session of standardised or personalised tACS in reducing EEG relative delta power in patients with delirium. Secondary objectives include assessment of the impact of daily standardised or personalised tACS compared with sham on the duration and/or severity of delirium, the length of hospital stay and cognitive functioning 3 months after the initial tACS session.

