### Study design and setting

This study is a double-blind, RCT conducted across three medical centres in the Netherlands: the University Medical Center (UMC) Utrecht, Radboud UMC and HagaZiekenhuis. To assess safety and feasibility of tACS in delirious patients, the study will start with a pilot phase in which 30 patients will be randomised in a 1:1 ratio to receive daily either standardised active tACS or sham treatment for a maximum of 14 days, or until resolution of delirium or hospital discharge.

On completion of the pilot phase, the main study phase will begin, introducing the personalised treatment arm. Criteria for continuing to the main study phase are defined under outcomes. All patients from the pilot phase will be included in the main study analyses. Randomisation weights will be recalculated, and participants will be allocated in an overall 1:1:1 ratio to receive either standardised tACS, personalised tACS, or sham treatment (ie, combining personalised sham and standardised sham tACS into one arm). The baseline visit will include delirium assessment using the Delirium Interview,^41^ administered by a trained researcher, and reviewed by an expert delirium panel. Furthermore, information will be collected from the electronic patient record and the Clinical Frailty Scale^42^ will be evaluated. After these assessments, the first treatment session starts which includes a 64-channel EEG measurement before and after the first tACS or sham treatment. Also, a questionnaire on sensation to assess possible adverse events (AEs) of tACS, a questionnaire on feasibility and questionnaire on blinding and subjective treatment experiences (online supplemental appendix 1) will be administered. Following this, daily tACS or sham treatment visits and delirium assessments will take place for a maximum of 14 days, or until resolution of delirium or hospital discharge, whichever comes first. To account for fluctuations in delirium symptoms, resolution of delirium is defined as two consecutive negative delirium assessments. The treatment phase will end with a close-out visit including a follow-up 64-channel EEG and administration of the questionnaires on sensation, blinding and subjective treatment experiences. A brief cognitive assessment using the Telephone Interview for Cognitive status, modified version (TICS-M)^43 44^ is planned at 3 months after the first tACS session. The study design is illustrated in figure 1, and the study schedule is presented in table 1.

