#### Patient withdrawal

If a patient and/or legal representative wants to withdraw from the study, they can do so without any consequences. We will adhere to the definitions and guidelines stipulated in the code of conduct relating to the expression of objection by incapacitated (psycho)geriatric patients in the context of the WMO (2002). The clinician or investigator can decide to withdraw a subject from the study for urgent medical reasons. There are no expected negative effects of prematurely ending the stimulation sequence.

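### SAEs are counted only to 24 hours after each patient's own last session, so observation time depends on treatment response and later events are not collected

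*Protocol article*

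**What the plan says.** All references are to the protocol article.

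- *Serious adverse events (SAEs)* lists the usual seriousness criteria and then makes timing part of the definition: the event must fall "within the timeframe of tACS treatment, which includes up to 24 hours after the last tACS session".
- *Study design and setting* fixes when sessions end. They run daily "for a maximum of 14 days, or until resolution of delirium or hospital discharge, whichever comes first", and "resolution of delirium is defined as two consecutive negative delirium assessments".
- *Patient withdrawal* adds two further ways for sessions to end: "If a patient and/or legal representative wants to withdraw from the study, they can do so without any consequences", and "The clinician or investigator can decide to withdraw a subject from the study for urgent medical reasons".
- *Adverse events* describes how events are found: "On each treatment day, the study team will screen the electronic patient record" and ask the treating staff about changes since the previous session.
- The Abstract states the hoped-for effect: "Hence, tACS offers a potential treatment for augmenting EEG activity and reducing the duration of delirium". *Study objectives* makes it a secondary aim: "assessment of the impact of daily standardised or personalised tACS compared with sham on the duration and/or severity of delirium".
- Table 1 has a post-treatment visit (V2), but neither it nor the text says how long after the last session V2 takes place. A telephone contact is planned 3 months after the first session; the SAE definition does not use it.

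**The concern.** The end of SAE observation is not a fixed time after randomisation. It is set by what happens to the patient afterwards: recovery, discharge or withdrawal. The trial hopes that active tACS brings recovery forward. An arm that recovers sooner is then observed for less time and accumulates fewer SAEs without being safer, so an effect on duration can look like a safety benefit. Separately, a patient whose last session comes early has no SAE collection beyond the following 24 hours, in whichever arm.

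This matters because safety and tolerability are the pilot's primary objective, the article says no earlier randomised trial has tested tACS for delirium, and no independent data monitoring committee is planned. The safety measure compared after the pilot looks only at the hour after stimulation. The SAE record is therefore the main stated source on later serious harm.

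**Working it through.** The article gives no SAE rate, expected count or mean treatment length, so there is no stated figure to reproduce. The check has three steps: the length of the window from the text, its effect on counts under assumed rates, and what an analysis could repair.

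**1. Length of the window.** With sessions on consecutive days, *k* sessions span *k* − 1 days, and the final 24 hours add one day:

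window = (*k* − 1) + 1 = *k* days.

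With *k* from 1 to 14, the window is about 1 to about 14 days.

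**2. Effect on counts at equal risk.** Inputs: 53 patients per arm (*Sample size and statistical power*). Assumed, because the article gives neither: a constant daily SAE hazard *h*, equal in both arms, and the number of treatment days *d* per arm.

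Proportion with at least one SAE in the window = 1 − exp(−*h* × *d*). With *h* = 0.01, and *d* = 8 on sham and 5 on active for every patient:

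- sham: 1 − exp(−0.08) = 7.7%, or 53 × 0.077 = 4.1 patients
- active: 1 − exp(−0.05) = 4.9%, or 53 × 0.049 = 2.6 patients

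The gap is about 1.5 patients per arm, with no difference in risk.

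Expected number of SAEs = 53 × *h* × *d*. The ratio between arms is the ratio of the windows, whatever the hazard:

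| Active vs sham days | h = 0.5% | h = 1% | h = 2% | h = 3% | Ratio |
|---|---|---|---|---|---|
| 7 vs 7 | 1.85 vs 1.85 | 3.71 vs 3.71 | 7.42 vs 7.42 | 11.13 vs 11.13 | 1.00 |
| 6 vs 7 | 1.59 vs 1.85 | 3.18 vs 3.71 | 6.36 vs 7.42 | 9.54 vs 11.13 | 0.86 |
| 5 vs 7 | 1.33 vs 1.85 | 2.65 vs 3.71 | 5.30 vs 7.42 | 7.95 vs 11.13 | 0.71 |
| 4 vs 8 | 1.06 vs 2.12 | 2.12 vs 4.24 | 4.24 vs 8.48 | 6.36 vs 12.72 | 0.50 |

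The first row shows the condition: with equal treatment length there is no distortion.

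**3. What analysis can and cannot repair.** A simulation with random stopping capped at 14 days and a 1% daily hazard gave mean windows of 4.8 and 6.2 days. The proportions with an SAE were 4.65% and 5.95%, but the rate was the same in both groups, 0.0101 per person-day. Dividing by time at risk therefore removes the artefact when the hazard is constant.

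It does not bring back uncollected events. Over a common 15 days (14 plus 24 hours) at 1% per day, 1 − exp(−0.15) = 13.9% of patients in each arm would have an SAE, or 53 × 0.139 = 7.4 patients. Under the present rule, in the 8-versus-5-day example, a first event after the window closes is missed in 13.9 − 7.7 = 6.2% of sham patients and 13.9 − 4.9 = 9.1% of active patients (from unrounded values).

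**The case against.** A short window after the last treatment is a common convention, and it is easy to defend for a 30-minute stimulation session in patients who have many unrelated complications. The article describes no formal between-arm SAE comparison; tabulation by arm, including rates per person-day, may be in an analysis plan that is not shown. The hazards and durations above are assumed, and a gap of about 1.5 patients in 53 is within chance variation.

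These points stand. They limit the size of the finding and rule out calling it a biased test. They do not change the collection rule, and an analysis plan cannot supply events that the protocol defines out of the SAE record.

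Two stronger readings are tempting, and the documents do not support them:

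- A reader might infer that nobody sees the patient after the last session. Table 1 schedules V2, with medication use, delirium scores and the sensation questionnaire. What can be said is narrower: V2's timing is not stated, and the record screen is described for treatment days only.
- A reader might infer that a patient who deteriorates after a session, is withdrawn and dies some days later is lost from the SAE count. A deterioration that serious would usually meet an SAE criterion inside the window, with the death as its outcome. What is lost is a separate event that begins after the 24 hours. *Patient withdrawal* also does not say that data collection stops.

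**Conclusion.** The concern holds in a limited form. As written, SAE observation runs from about 1 to about 14 days per patient and depends on response, discharge and withdrawal. Counts by arm are not comparable whenever mean treatment length differs. If active tACS shortens delirium, the error favours the active arms; if it prolongs treatment, the error goes the other way; if length is equal, there is none. The illustrative 7.7% versus 4.9% rests on an assumed hazard of 1% per day, constant and equal in both arms, and on assumed durations of 8 and 5 days. The loss of events that begin more than 24 hours after an early last session does not depend on any difference between arms.

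The primary EEG outcome is unaffected. This is a weakness in safety data collection, worth correcting because the remedy is cheap and must be in place while data are being collected.

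**What to change.** In *Serious adverse events (SAEs)*, collect SAEs over one common window from the first session, for example the 14-day maximum treatment period plus 24 hours, whatever the date or reason of the last session. Apply it to all randomised patients who have not withdrawn consent to data collection. Complete it with one check of the electronic record at the end of the window, or a call if the patient has been discharged.

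Report all-cause death by arm up to the 3-month contact, which is already planned. Keep the count to 24 hours after the last session as a supportive on-treatment summary, with rates per person-day.

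No treatment or stopping rule changes. The cost is revised protocol wording, one record check or call per patient, and more SAE reports, many of them unrelated to tACS.

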### Data management, monitoring and access

The handling of personal data will adhere to the EU General Data Protection Regulation and the Dutch Act on Implementation of the General Data Protection Regulation. Study data will be collected and managed using Castor EDC, a secure electronic case record form (eCRF) accessible via the internet. Investigators will be assigned personal usernames and passwords, and all data transfers will be encrypted. Only data essential to addressing the research question outlined in this protocol will be collected and stored. All data will be pseudonymised and treated confidentially. Only necessary study members will have access to this subject identification list. Investigators will electronically sign to confirm that eCRF entries are accurate and complete. Source documents will be securely stored in a locked filing cabinet, accessible only to authorised research personnel, and archived for the legally mandated period. Before the start of the study, it is agreed which documents serve as source data for eCRF. Monitoring will be conducted in accordance with national laws and International Conference on Harmonisation-Good Clinical Practice (ICH-GCP) guidelines. Given the low-risk intervention, there will not be an independent data monitoring committee.

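### Infections, haemorrhage and laboratory disturbances are excluded from SAEs by event type and are not systematically counted by arm, so the sham comparison cannot test the assertion that they are unrelated to tACS

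*Protocol article*

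**What the plan says.** The Serious adverse events section opens with a definition based on seriousness alone: "An SAE is any untoward medical occurrence or effect that", followed by the usual outcomes (death, threat to life, hospitalisation or its prolongation, disability, other important events). The window is the tACS treatment period plus 24 hours after the last session.

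The same section then takes out a class of events, "infectious diseases such as pneumonia, wound infection, sepsis, (postoperative) haemorrhage, or laboratory disturbances, such as hyponatraemia or hypokalaemia", and says that those "that may prolong inpatients’ hospitalisation or may be life threatening, will not be considered as an SAE". The reason follows: "This exclusion is due to the frequency of these complications in the population being studied, which is unrelated to tACS treatment".

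The Adverse events section defines AEs broadly, "whether or not considered related to the experimental intervention", but limits what goes on the case report form to AEs that may be study-related. On each treatment day "the study team will screen the electronic patient record and consult with the treating physician or nurse about any health changes", and an event found this way becomes an AE if it is potentially related to study procedures.

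Three other statements bear on the point:

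- Under Study objectives, for the pilot phase "the primary objective is to evaluate the safety and tolerability of tACS in patients with delirium".
- Under Interim analysis, the pilot results on completed sessions, increased care requirements within 1 hour and delirium duration go to the Medical Research Ethics Committee (MREC) before the main phase.
- Under Data management, monitoring and access, "there will not be an independent data monitoring committee", because the intervention is considered low-risk.

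**The concern.** A high background rate is a sound reason not to send individual reports of common complications. It is not a reason to leave them out of a randomised comparison. That complications are common in this population says nothing about whether tACS leaves their frequency unchanged. The Introduction states that no randomised trial has studied tACS as a treatment for delirium, so this trial's sham arm is the available means of testing relatedness. The exclusion settles the question beforehand, by event type and not case by case.

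The article's own AE list shows why this is more than a formality. It treats falls out of bed, self-removal of a line, tube or drain, and increased antipsychotic use as possibly study-related. A haemorrhage or infection that followed such an event would belong to the excluded class, so the trigger could be recorded while its serious consequence was not an SAE.

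At stake is a group of potentially life-threatening events for which, under the text shown, neither the MREC at the pilot review nor the reader of the final report would see numbers by arm.

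**Working it through.** The plan states no figure on this point, so there is none to reproduce. The check has two parts.

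**1. Can the events reach a by-arm table by any stated route?**

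| Route | What it would capture | By-arm count of these complications? |
|---|---|---|
| SAE reporting | Listed events excluded when stay-prolonging or life threatening; death is not named in the exclusion, so fatal cases may still count | No (possibly fatal cases only) |
| AE reporting | Only events judged potentially study-related | No; depends on individual judgement, against a stated presumption |
| Pilot outcomes | Intervention, fixation or transfer to more advanced care within 1 hour of tACS | No; any cause, short window, pilot only |
| Length of stay (secondary outcome) | Total days in hospital | No; any cause |
| Table 1 | Medication use at every visit; physical health at baseline and follow-up | No; indirect trace only |
| Statistical analysis and Interim analysis sections | Efficacy, blinding, completed sessions, care requirements, delirium duration | No |

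No route gives a systematic count by arm.

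**2. What would recording them show?**

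*Arm sizes.* The pilot has 30 patients at 1:1, so about 15 active and 15 sham. The main phase has 129 at weights 3, 4, 1 and 2 (standardised active, personalised active, standardised sham, personalised sham), so 7/10 active and 3/10 sham.

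- Active: 15 + 0.7 × 129 = 105.3, about 105.
- Sham: 15 + 0.3 × 129 = 53.7, about 54.

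*Event rates.* The documents give none. The rates below are assumptions.

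*Formula.* Two-sided 5% normal approximation for two proportions, with d the difference, S₁ the unpooled and S₀ the pooled standard error:

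- pooled null variance: power = Φ((d − 1.96 × S₀)/S₁)
- unpooled variance throughout: power = Φ(d/S₁ − 1.96)

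*Worked case, sham 20% v active 40%, 54 v 105.*

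- S₁ = √(0.2×0.8/54 + 0.4×0.6/105) = 0.0724
- pooled rate = (54×0.2 + 105×0.4)/159 = 0.332; S₀ = √(0.332×0.668×(1/54 + 1/105)) = 0.0789
- pooled: Φ((0.20 − 0.1546)/0.0724) = Φ(0.63) ≈ 73%
- unpooled: Φ(0.20/0.0724 − 1.96) = Φ(0.80) ≈ 79%

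| Assumed rates (sham v active) | 54 v 105 |
|---|---|
| 20% v 40% | about 73–79% |
| 10% v 20% | about 35–42% |
| 20% v 30% | about 26–29% |

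For the pilot alone (15 v 15), 20% v 40% has about 22% power.

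*Precision.* With a common rate p in both groups, the 95% half-width for the risk difference is 1.96 × √(p(1−p)(1/105 + 1/54)): about 7 points at p = 5%, 10 at 10%, 13 at 20% and 15 at 30%. A large imbalance would be visible; a moderate one could easily be missed.

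**The case against.** The strongest reply has four parts.

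*The stated reason is frequency.* The clause on unrelatedness can be read as describing the background frequency, not as declaring every individual event unrelated. This stands as a point about wording: the reason is frequency together with asserted unrelatedness, not unrelatedness alone. The exclusion operates the same way under either reading.

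*Not being an SAE is different from not being recorded.* A reader might infer that these events vanish altogether. The documents do not support that. A complication judged potentially related is still an AE, a fatal case may still be an SAE, and the indirect traces tabulated above remain. What survives of the concern is narrower: none of these is a systematic count by arm.

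*Oversight exists.* The MREC approved the study and sees pilot results before the main phase. That is so, but the results listed for that review do not include these complications.

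*Recording would settle little.* Power is respectable only for a 20-point rise and is low in the pilot. In addition, infection and surgery are precipitants of delirium and enrolled patients already have causes under treatment, so some of these conditions will pre-date randomisation and are not lost safety data. Both points stand. They limit the claim to a descriptive gain and mean that the record should cover only new or worsening events. They do not justify having no count, since safety tables are ordinarily read descriptively.

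**Conclusion.** The concern holds in limited form. The article states a categorical rule, so this is not a matter of detail left to a fuller document. Together with the AE recording rule, it leaves infections, haemorrhage and laboratory disturbances without a systematic count by arm in a trial whose pilot has safety as part of its primary objective and which has no data monitoring committee. The assertion about tACS is therefore one that the trial's own comparison cannot check.

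The size of the loss cannot be stated from the documents, because they give no event rates. Under the assumed rates, a by-arm count would probably expose a doubling from 20% to 40% across the whole trial and would have low power for 10-point rises. What is lost is chiefly a descriptive table.

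A reader might also infer that tACS raises the risk of these complications, or that the efficacy results are affected. The documents support neither: they hold no safety data, and the rule does not touch the primary or secondary efficacy estimates. The change is worth making because it is cheap and the trial is still recruiting.

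**What to change.** Keep the exemption of the listed complications from SAE and expedited reporting. Then:

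- Record in the eCRF, for all arms and regardless of judged relatedness, each listed complication that is new or worsens after randomisation and falls within the existing SAE window: event, date, seriousness.
- Tabulate these by arm at the pilot review sent to the MREC and in the final report, as a descriptive comparison.
- Remove the advance assertion that they are unrelated to tACS and give background frequency as the reason for the reporting exemption.
- State whether a fatal listed complication counts as an SAE, since the exclusion does not mention death.

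The cost is a short checklist, one table and a minor amendment. Staff already screen the record and consult the treating team each treatment day, so the added work is mainly data entry. For patients already treated, back-entry from the patient record should be possible.
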